|                             | placebo depending on body weight and treatment assignment.                                                                                                                                                                                                                                                                                                                                                                                                                                                                                                                                                                                                                                                                                                                                                                                                                                                                                                                                                                                                                                                       |
| Safety Evaluation    | Vital signs, ECGs, physical examinations (including a neurologic examination), ocular examinations, AEs, serum chemistries, hematology studies, prothrombin times, and urinalyses.                                                                                                                                                                                                                                                                                                                                                                                                                                                                                                                                                                                                                                                                                                                                                                                                                                                                                                                               |
| Efficacy Evaluation  | 
Efficacy evaluations (skin snips) will be performed at day 8, 1 month (<math>\pm 1</math> week), 2 months (<math>\pm 1</math> week), 3 months (<math>\pm 1</math> week), 6 months (<math>\pm 1</math> month), 12 months (<math>\pm 1</math> month) and 18 months (<math>\pm 1</math> month) after dosing and the number of microfilariae/mg of skin determined. Evaluation of the viability and fertility of the adult worms will occur at 18 months. All located nodules will be excised at 18 months, processed for histopathology, and slides interpreted by one or more observers. Microfilarial migration into blood and urine will be used as indirect evidence of the speed of microfilaricidal activity.
 
All subjects who have skin microfilariae at the 18-month visit will be treated with the approved dosage of ivermectin.
                                                                                                                                                                                                                                                            |
| Pharmacokinetics     | 
Blood samples for determination of moxidectin plasma concentrations will be collected within 2 hours prior to dosing (0 hr), and at 1, 2, 4, 8, 24, and 72 hours after study drug administration and on study days 8, 13, 18, 1 month (<math>\pm 1</math> week), 2 months (<math>\pm 1</math> week), 3 months (<math>\pm 1</math> week), 6 months (<math>\pm 1</math> month), and 12 months (<math>\pm 1</math> month). Pharmacokinetic (PK) samples will be drawn from all subjects in all cohorts with the exception of the 2nd group of 16 subjects with <math>>20</math> microfilariae/mg of skin in cohorts 3, 6, and 9. Samples from subjects will be analyzed by a validated bioanalytical method.
 
A PK analysis will be performed using model independent methods to characterize the PK parameters of moxidectin, such as maximum plasma concentration (<math>C_{max}</math>), time to reach the maximum plasma concentration (<math>t_{max}</math>), area under the plasma concentration vs. time curve (AUC) and the apparent terminal elimination half-life (<math>t_{1/2}</math>).
 |
| Pharmacodynamics     | Analysis of a correlation between PK parameters, gender, severity of infection, efficacy, and efficacy-related AEs.                                                                                                                                                                                                                                                                                                                                                                                                                                                                                                                                                                                                                                                                                                                                                                                                                                                                                                                                                                                              |
| Statistical Analysis | 
This is a randomized, double blind, active-control, dose-escalation trial comparing 3 doses of moxidectin (2, 4, and 8 mg) with ivermectin, stratified by microfilariae density (mild, moderate, severe) and gender. Subjects will be treated as inpatients for the first 18 days and as outpatients for the remainder of the 18-month study.
 
The primary analysis population for safety will be the modified intent-to-treat (mITT) population, which consists of all subjects who receive study
                                                                                                                                                                                                                                                                                                                                                                                                                                                                                                                                                                                                  |

---

medication. For efficacy, the primary analysis population will be the evaluable subject population, which is defined as all subjects who receive study medication and have baseline and 18 month microfilariae count data. An mITT sensitivity analysis will also be performed to evaluate the effect on the efficacy results of dropouts occurring before 18 months. The primary objective of the study is to evaluate the safety of escalating moxidectin regimens. Both the incidence of clinical AEs and clinically significant laboratory test results will be used to assess safety. The primary efficacy endpoint is the reduction from baseline in skin microfilariae at 18 months. Microfilariae count will be defined as the geometric mean of skin microfilariae/mg taken at 4 sites (iliac crests and calves).

In addition, important secondary endpoints are the reduction from baseline in skin microfilariae at 8 days, 1 month, 2 months, 3 months, 6 months, and at 12 months, area under the curve (calculated by using the trapezoidal method through the 18-month visit), ocular examination (time of maximum reduction of microfilariae and number (%) of subjects with complete clearance) and nodulectomy (viability and fertility of macrofilariae) at 18 months.

---

**Rationale for Number of  
Subjects**

At each dose level, 16 mildly, 16 moderately and 32 severely infected subjects will be treated with moxidectin or ivermectin in a 3:1 ratio. The probability of detecting at least 1 AE of grade 2 or higher among 12 moxidectin-treated subjects will be 0.114 and 0.718 when the true rates are 1% and 10%, respectively. The probability of detecting at least 1 AE of grade 2 or higher among 24 moxidectin-treated subjects will be 0.214 and 0.92 when the true rates are 1% and 10%, respectively.

---

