### 14.3 Prohibited Treatment

Smoking, the ingestion of alcoholic beverages, grapefruit, or grapefruit juice, and the use of non-prescribed drugs will not be permitted during the 18 day admission period. Treatment with other anthelmintic agents including ivermectin will be prohibited for the duration of the study. If anthelmintic treatment has been taken for any reason, the subject will be withdrawn from the study.

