#### **19.1.2 Secondary**

Secondary efficacy variables will include:

- The mean reduction from baseline, as well as the percentage of subjects with undetectable microfilariae, will be calculated by dose and severity of infection for each post treatment evaluation time point.
- The change from baseline in the mean number of skin microfilariae per milligram of skin sampled at 4 body locations (right and left iliac crests, right and left calves) at 12 months after test article administration.

- The change from baseline in the mean number of skin microfilariae per milligram of skin sampled at day 8, 1 month, 2 months, 3 months, and 6 months.
- The change from trough values to 12 months and 18 months post treatment in the mean number of skin microfilariae per milligram of skin sampled at 4 body locations (right and left iliac crests, right and left calves) to quantify the effect on the reproductive capacity of adult worms.
- The area under the curve (calculated by using the trapezoidal method through the 18 month visit)
- Ocular examination (time of maximum reduction of microfilariae and number (%) of subjects with complete clearance). The change from baseline in the mean number of ocular microfilariae measured in the anterior chamber. Living and dead microfilariae in the cornea and punctate opacities will also be counted. Retinal changes secondary to the disease will also be examined. Ocular examinations will be performed at baseline and on days 3 or 4, 7 or 8, 14 or 15, and at 1 month, 3 months, 6 months, 12 months and 18 months.
- Evidence of an effect on the viability and/or fertility of the macrofilaria will be obtained from the histologic examination of nodules excised at 18 months. Parameters to be evaluated include:
  - a. Viability (number live, moribund, dead)
  - b. Calcification (presence/absence)
  - c. Reproductive status:
    - i. Females:
      - Proportion:
        - 1. Number producing embryos up to the microfilarial stage
        - 2. Degenerated microfilariae in uterus
        - 3. Relict embryos
    - ii. Males:
      - Proportion with:
        - 1. Spermatogenesis normal or abnormal
    - iii. Other criteria:
      - Proportion of nodules with:
        - 1. Microfilariae in the capsule
        - 2. No male worms

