## **21. STATISTICAL ANALYSIS**

### **21.1 Statistical Methods**

This is a randomized, double-blind, active-control, dose-escalation trial comparing 3 doses of moxidectin (2, 4, and 8 mg) with ivermectin, stratified by microfilariae density (mild, moderate, severe) and gender. Subjects will be treated as in subjects for the first 18 days and as outpatients for the remainder of the 18 month study.

The primary analysis population for safety will be the modified intent-to-treat (mITT) population, which consists of all subjects who receive study medication. For efficacy, the primary analysis population will be the evaluable subject population, which is defined as all subjects who receive study medication and have baseline and 18-month microfilariae count data. An mITT sensitivity analysis will also be performed to evaluate the effect on the efficacy results of dropouts occurring before 18 months.

The primary objective of the study is to evaluate the safety of escalating moxidectin regimens. Both the incidence of clinical AEs and clinically significant laboratory test results will be used to assess safety.

The primary efficacy endpoint is the reduction from baseline in skin microfilariae at 18 months. Microfilariae count will be defined as the geometric mean of skin microfilariae/mg taken at 4 sites (iliac crests and calves).

In addition, important secondary endpoints are the reduction from baseline in skin microfilariae load at day 8, 1 month, 2 months, 3 months, 6 months and 12 months, area under the curve (calculated by using the trapezoidal method through the 18 month visit), ocular examination (time of maximum reduction of microfilariae and number (%) of subjects with complete clearance) and nodulectomy (viability and fertility of macrofilariae) at 18 months.

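### The day-8 to month-12 skin endpoints and the ocular efficacy endpoints inherit a primary population that requires an 18-month skin count they do not need

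*Supplement*

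**What the plan says.** Section 21.1 (Statistical Methods) of the latest protocol version sets the population by purpose: "For efficacy, the primary analysis population will be the evaluable subject population". To belong to it, a dosed subject must "have baseline and 18-month microfilariae count data". The synopsis repeats the rule, naming the "evaluable subject population, which is defined as all subjects who receive study medication and have baseline and 18 month microfilariae count data". Safety has its own population, mITT, which is everyone dosed.

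The synopsis then states that "important secondary endpoints are the reduction from baseline in skin microfilariae at 8 days, 1 month, 2 months, 3 months, 6 months" and at month 12. It adds AUC through month 18, two ocular efficacy endpoints (time of maximum reduction, complete clearance) and nodulectomy at month 18. No population is attached to any of these.

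Section 19.1.2 says that mean reduction and percent undetectable "will be calculated by dose and severity of infection for each post treatment evaluation time point", again without naming a population. Sections 19.2, 21.2 and 21.3 name none either.

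One further analysis is promised: "An mITT sensitivity analysis will also be performed to evaluate the effect on the efficacy results of dropouts occurring before 18 months". How missing values are handled in it is not described.

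**The concern.** The early endpoints do not need a month-18 skin snip. Day-8 snips are taken while subjects are inpatients (15.1.10; discharge is on day 18, 15.1.20). Section 19.2 bases the maximal microfilaricidal effect on the day-8 and month-1 snips. The ocular endpoints come from eye examinations that start on day 3 or 4. Yet under a rule stated for efficacy as a whole, someone with complete skin and eye data through month 12 leaves the primary analysis of all those endpoints if the month-18 snip is missing.

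This is a different question from how to treat a missing month-18 value. At the earlier visits the data exist, and they are set aside because of a later event.

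At stake is secondary objective 1 (11.2), the dose effect on skin microfilariae from day 8 onward. Precision is lost without need, and the early comparison is made in a subset defined after treatment. The protocol contains one route by which leaving could be tied to outcome: "If anthelmintic treatment has been taken for any reason, the subject will be withdrawn from the study" (14.3).

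**Working it through.** **Plan's own denominators.** At 3:1, each moxidectin dose has 12 + 12 + 24 = 48 subjects. Ivermectin has (4 + 4 + 8) × 3 = 48. The total is 3 × 48 + 48 = 192. This reproduces section 21.3.

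**Subjects affected.** The documents give no loss rate, so 5%, 10%, 15% and 20% by month 18 are assumed. Loss × 192 gives about 10, 19, 29 and 38 subjects without a month-18 count. At day 8 nearly all of them would have been observed.

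**Precision near day 8.** If all leavers had the early count, interval width grows by 1/√(1 − loss) − 1:

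| Loss by month 18 | Kept per 48 | Widening |
|---|---|---|
| 5% | 45.6 | 2.6% |
| 10% | 43.2 | 5.4% |
| 15% | 40.8 | 8.5% |
| 20% | 38.4 | 11.8% |

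**Precision at month 12.** A subject who left before month 12 has no month-12 count under either rule. A visit-specific population recovers only those lost between months 12 and 18. If half of the loss has occurred by month 12 (an assumption), the widening is √[(1 − loss/2)/(1 − loss)] − 1. That is √(0.95/0.90) − 1 = 2.7% at 10% loss and √(0.90/0.80) − 1 = 6.1% at 20%. The table is therefore a ceiling that falls with time.

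**Selection, clearance scale.** Suppose true early clearance p is equal in both arms, 5% of moxidectin subjects leave whatever their status, and 5% of cleared but 20% of uncleared ivermectin subjects leave. Ivermectin clearance among those kept is 0.95p/[0.95p + 0.80(1 − p)]:

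- p = 50%: 0.475/0.875 = 54.3%, so moxidectin minus ivermectin is −4.3 points
- p = 70%: 0.665/0.905 = 73.5%, difference −3.5 points
- p = 90%: 0.855/0.935 = 91.4%, difference −1.4 points

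If leaving is unrelated to clearance, or depends on it in the same way in both arms, the difference stays 0 in these equal-rate examples.

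**Selection, count scale.** Assume an SD of 0.8 on log10 counts and a correlation ρ between the early and the late count. Removing the top fraction q by late count multiplies the early geometric mean by 10^(−0.8 × ρ × φ(z)/(1 − q)), where z is the cut-off. The term φ(z)/(1 − q) is 0.195 at q = 10% and 0.350 at q = 20%. The factors are 0.78 and 0.64 at ρ = 0.7, and 0.87 and 0.77 at ρ = 0.4.

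A milder pattern has the upper half twice as likely to leave. At 10% loss (13.3% against 6.7%) the shift in the late count is 0.798 × 0.0667/(2 × 0.9) = 0.030 SD. At 20% loss (26.7% against 13.3%) it is 0.798 × 0.1333/(2 × 0.8) = 0.067 SD. The factors are then about 0.96 and 0.92 at ρ = 0.7, and 0.98 and 0.95 at ρ = 0.4.

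**The case against.** The strongest reply is that the remedy is largely planned already. The mITT sensitivity analysis covers all dosed subjects, and at an early visit it can use every observed count. A reader might infer that the early data of later leavers are thrown away; they are not. What stands is that the primary result for these endpoints still rests on the restricted set, and that the mITT method is unstated.

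Second, no sentence assigns the 18-month rule to each secondary endpoint, and the sponsor may have meant it for month 18 only. That is possible, but the wording covers efficacy generally and no other population is offered. If the narrower meaning was intended, one clause settles it.

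Third, the route to bias is thin. Withdrawal follows anthelmintic use for whatever reason. Section 12 describes an area outside ivermectin distribution where most villages had not heard of the drug at first contact, although communities were told it could be had at nearby centres. A reader might infer that high counts will vanish mainly from the less effective arm; nothing in the documents shows this. The factors of 0.64–0.87 assume that the leavers are exactly the highest ivermectin counts with no matching moxidectin loss, and they ignore the covariate adjustment in 21.2. They are an extreme illustration, not an estimate.

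Fourth, section 15.2 asks early terminators to undergo the month-18 procedures, which include skin snips. Whether such a snip makes the subject evaluable is left open, and it does not help with subjects who simply do not return.

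Fifth, the consequences are limited. The primary objective is safety, analysed in mITT. Ocular safety findings also fall under mITT, so only ocular efficacy is affected. Dose progression (18.2) uses data from all previously enrolled cohorts.

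**Conclusion.** The point holds in limited form. As written, the primary analyses of the day-8 to month-12 skin endpoints and of the ocular efficacy endpoints leave out subjects who were observed for those endpoints but lack an 18-month skin count. The precision cost is at most 2.6–11.8% in interval width for an assumed 5–20% loss; this is an upper bound near day 8 and is smaller at month 12. Bias requires leaving that is related to outcome and differs by arm. The documents give no loss rate, SD or correlation from which to size it, so they do not support a claim that the early comparisons will be biased, or by how much. AUC through month 18 and nodulectomy properly need month-18 data and are not at issue. This is a cheap improvement to secondary efficacy analyses, not a flaw in the primary objective.

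**What to change.** In section 21.1 and the synopsis:

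- Limit the 18-month requirement to endpoints that need month-18 data: the 18-month count, AUC through month 18, and nodulectomy.
- For each earlier skin visit, analyse all dosed subjects with a baseline count and a count at that visit.
- For the ocular efficacy endpoints, analyse all dosed subjects with the relevant eye examinations, and say which examinations those are.
- Show the 18-month-evaluable subset as the sensitivity analysis for these endpoints.
- State whether a skin snip taken at a termination visit under section 15.2 counts as 18-month data.

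For the skin counts, one repeated-measures model on the log scale with a treatment-by-visit term would serve equally well.

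The cost is a few sentences of wording, with no new subjects, visits or procedures. The small downside is that the number analysed differs by visit and must be tabulated.

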## 8. SUBJECT FLOWCHART

|                                                                            | Visit Number |    |                |   |   |   |   |   |   |    |    |    |    |    |    |    |    |    |    |    |               |               |               |               |                |                |
|----------------------------------------------------------------------------|--------------|----|----------------|---|---|---|---|---|---|----|----|----|----|----|----|----|----|----|----|----|---------------|---------------|---------------|---------------|----------------|----------------|
| Clinical Planned Events                                                    | 1            | 2  | 3              | 4 | 5 | 6 | 7 | 8 | 9 | 10 | 11 | 12 | 13 | 14 | 15 | 16 | 17 | 18 | 19 | 20 | 21            | 22            | 23            | 24            | 25             | 26             |
|                                                                            | Study Day    |    |                |   |   |   |   |   |   |    |    |    |    |    |    |    |    |    |    |    |               |               |               |               |                |                |
| Study Procedures                                                           | -4 to
-2  | -1 | 1              | 2 | 3 | 4 | 5 | 6 | 7 | 8  | 9  | 10 | 11 | 12 | 13 | 14 | 15 | 16 | 17 | 18 | 1 mo
±1 wk | 2 mo
±1 wk | 3 mo
±1 wk | 6 mo
±1 mo | 12 mo
±1 mo | 18 mo
±1 mo |
| Informed consent a                                              | X            |    |                |   |   |   |   |   |   |    |    |    |    |    |    |    |    |    |    |    |               |               |               |               |                |                |
| Demographics                                                               | X            |    |                |   |   |   |   |   |   |    |    |    |    |    |    |    |    |    |    |    |               |               |               |               |                |                |
| Admission                                                                  | X            |    |                |   |   |   |   |   |   |    |    |    |    |    |    |    |    |    |    |    |               |               |               |               |                |                |
| Medical history                                                            | X            |    |                |   |   |   |   |   |   |    |    |    |    |    |    |    |    |    |    |    |               |               |               |               |                |                |
| Medication history                                                         | X            |    |                |   |   |   |   |   |   |    |    |    |    |    |    |    |    |    |    |    |               |               |               |               |                |                |
| Physical examination                                                       | X            |    |                |   |   |   |   |   |   |    |    |    |    |    |    |    |    |    |    |    | X             | X             | X             | X             | X              | X              |
| Height                                                                     | X            |    |                |   |   |   |   |   |   |    |    |    |    |    |    |    |    |    |    |    |               |               |               |               |                |                |
| Weight                                                                     | X            |    | X              | X | X | X | X | X | X | X  | X  | X  | X  | X  | X  | X  | X  | X  | X  | X  | X             | X             | X             | X             | X              | X              |
| Vital signs                                                                | X            | X  | X              | X | X | X | X | X | X | X  | X  | X  | X  | X  | X  | X  | X  | X  | X  | X  | X             | X             | X             | X             | X              | X              |
| ECG                                                                        | X            |    | X b | X | X |   |   |   |   | X  |    |    |    |    |    |    |    |    |    |    |               |               |               |               |                |                |
| Ocular examination                                                         | X            |    |                |   | X |   |   |   | X |    |    |    |    |    |    | X  |    |    |    |    | X             | X             | X             | X             | X              | X              |
| Retinal Colour
Photographs and
Fluorescein
angiogram c | X            |    |                |   |   | X |   |   |   | X  |    |    |    |    |    | X  |    |    |    |    | X             | X             | X             | X             | X              | X              |
| Interim physical
examination                                            |              |    | X              | X | X | X | X | X | X | X  | X  | X  | X  | X  | X  | X  | X  | X  | X  |    |               |               |               |               |                |                |
| Hematology d                                                    | X            |    | X              | X |   | X |   |   |   | X  |    |    |    |    | X  |    |    |    |    | X  | X             | X             | X             | X             | X              | X              |
| Serum chemistry                                                            | X            |    | X              | X |   | X |   |   |   | X  |    |    |    |    | X  |    |    |    |    | X  | X             | X             | X             | X             | X              | X              |
| Pregnancy test                                                             |              | X  |                |   |   |   |   |   |   |    |    |    |    |    |    |    |    |    |    |    |               |               |               |               |                |                |
| Urinalysis d                                                    | X            |    | X              | X |   | X |   |   |   | X  |    |    |    |    | X  |    |    |    |    | X  | X             | X             | X             | X             | X              | X              |
| Clinical Planned Events                                                    | 1            | 2  | 3              | 4 | 5 | 6 | 7 | 8 | 9 | 10 | 11 | 12 | 13 | 14 | 15 | 16 | 17 | 18 | 19 | 20 | 21            | 22            | 23            | 24            | 25             | 26             |

- ~~Will~~Informed consent will be obtained in the village prior to transport of potential study participants to the study centre and before any study-related procedures are performedadmission. Informed consent may be obtained prior to day -4.
- ECG to be done approximately 4 hours after study drug administration. Can be repeated on days 4 through 7 if clinically indicated.
- For all subjects until month 3, then only in subjects with lesions or visual defects.
- All blood and urine samples will be filtered and stained for microfilariae.

| SUBJECT FLOWCHART (Continued)       |              |                |                |   |   |   |   |   |   |    |    |    |    |    |    |    |    |    |    |    |               |               |               |                |                |                |
|-------------------------------------|--------------|----------------|----------------|---|---|---|---|---|---|----|----|----|----|----|----|----|----|----|----|----|---------------|---------------|---------------|----------------|----------------|----------------|
|                                     | Visit Number |                |                |   |   |   |   |   |   |    |    |    |    |    |    |    |    |    |    |    |               |               |               |                |                |                |
| Clinical Planned Events             | 1            | 2              | 3              | 4 | 5 | 6 | 7 | 8 | 9 | 10 | 11 | 12 | 13 | 14 | 15 | 16 | 17 | 18 | 19 | 20 | 21            | 22            | 23            | 24             | 25             | 26             |
|                                     | Study Day    |                |                |   |   |   |   |   |   |    |    |    |    |    |    |    |    |    |    |    |               |               |               |                |                |                |
| Study Procedures                    | -4 to
-2  | -1             | 1              | 2 | 3 | 4 | 5 | 6 | 7 | 8  | 9  | 10 | 11 | 12 | 13 | 14 | 15 | 16 | 17 | 18 | 1 mo
±1 wk | 2 mo
±1 wk | 3 mo
±1 wk | 6 mo ±
1 mo | 12 mo
±1 mo | 18 mo
±1 mo |
| Skin snips                          | X            |                |                |   |   |   |   |   |   | X  |    |    |    |    |    |    |    |    |    |    | X             | X             | X             | X              | X              | X              |
| Randomization                       |              | X              |                |   |   |   |   |   |   |    |    |    |    |    |    |    |    |    |    |    |               |               |               |                |                |                |
| Drug packaging
and dispensing    |              | X              |                |   |   |   |   |   |   |    |    |    |    |    |    |    |    |    |    |    |               |               |               |                |                |                |
| Double-blind drug
administration |              |                | X e |   |   |   |   |   |   |    |    |    |    |    |    |    |    |    |    |    |               |               |               |                |                |                |
| Moxidectin Plasma
Samples        |              | X f | X g | X |   | X |   |   |   | X  |    |    |    | X  |    |    |    |    |    | X  | X             | X             | X             | X              | X              |                |
| Adverse events                      | X            | X              | X              | X | X | X | X | X | X | X  | X  | X  | X  | X  | X  | X  | X  | X  | X  | X  | X             | X             | X             | X              | X              | X              |
| DMPA h                   |              |                |                |   |   |   |   |   |   |    |    |    | X  |    |    |    |    |    |    |    |               | X             |               |                |                |                |
| Discharge                           |              |                |                |   |   |   |   |   |   |    |    |    |    |    |    |    |    |    |    | X  |               |               |               |                |                |                |
| Nodulectomy                         |              |                |                |   |   |   |   |   |   |    |    |    |    |    |    |    |    |    |    |    |               |               |               |                |                | X i |
| Clinical Planned Events             | 1            | 2              | 3              | 4 | 5 | 6 | 7 | 8 | 9 | 10 | 11 | 12 | 13 | 14 | 15 | 16 | 17 | 18 | 19 | 20 | 21            | 22            | 23            | 24             | 25             | 26             |

e. Will be given after an overnight fast and 2 hours before breakfast.

f. Day -1 sample will be taken approximately 2 hours before drug administration.

g. Day 1 samples will be taken at 1, 2, 4, and 8 hours after drug administration.

h. Depo-medroxyprogesterone acetate (DMPA) on women of childbearing potential not ~~protected by Norplant system~~ already receiving a parenterally administered contraceptive.

i. All located nodules will be processed for histopathology and slides read by 1 or more blinded observers.

